#### Data analysis

The protocol is designed to examine relative differences across yawning stimulus conditions and within-subject changes over time, rather than to establish yawning-specific causal effects relative to neutral stimulus exposure. As such, findings will be interpreted in terms of associations with yawning stimulus exposure and relative differences across conditions, rather than as evidence of yawning-specific causal effects.

The primary outcome will be the change in subjective sleepiness, as assessed using post-condition KSS ratings. Analyses will focus on within-subject changes in KSS across experimental conditions, as well as changes relative to baseline measurements.

Secondary outcomes will include physiological markers associated with sleepiness and arousal, including autonomic nervous system activity (e.g., HRV, EDA), skin temperature variation, pupil size dynamics, and neural activity patterns associated with reduced alertness. These measures are selected based on prior literature demonstrating their sensitivity to changes in vigilance and alertness. For example, HRV has been shown to increase with sleepiness and reduced vigilance, often reflecting shifts toward parasympathetic dominance, particularly in low-frequency bands [45,46]. Similarly, pupillary measures such as the PUI have also been associated with increased sleepiness and reduced alertness [47,48]. In addition, decreases in oxygenated and total hemoglobin in prefrontal regions, as measured by fNIRS, have been linked to fatigue and reduced alertness [49].

While these physiological measures have been widely used as indices of arousal and vigilance, they are not universally established as direct measures of subjective sleepiness. Accordingly, these measures will be interpreted as complementary indicators of arousal-related processes in conjunction with subjective and behavioral measures. Analytical focus will therefore be placed on changes in physiological signals relative to baseline and on their associations with subjective sleepiness, rather than attempting to derive a single direct physiological measure of sleepiness.

Exploratory outcomes will include behavioral indicators of sleepiness, such as yawning occurrence and instances of sleep onset observed during the experiment. Additional exploratory analyses will examine the relationship between yawning behavior and both subjective and physiological outcomes. These relationships will be modeled using mixed-effect approaches where appropriate, which allows for the inclusion of both within-subjects (e.g., condition, time) and between-subjects (e.g., chronotype, baseline sleep quality) factors.

Statistical significance will be evaluated using two-sided tests with an alpha level of 0.05 unless otherwise specified. Results will be reported using effect sizes (e.g., estimated mean differences as quantified by Cohen’s *d* or Hedge’s *g*) alongside 95% confidence intervals and p-values. Given the exploratory nature of several outcomes, findings will be interpreted with appropriate caution, and emphasis will be placed on the direction, magnitude, and consistency of observed effects rather than statistical significance alone. The data analysis plan is summarized in Table 2.

**Table 2 tbl0002:** Data analysis plan.

Analysis Level	Procedure
Primary outcome analysis	▪ Analyze changes in KSS using linear mixed-effects models to account for the within-subject repeated-measures design ▪ Fixed effects will include stimulus type (human vs digital character yawning), auditory condition (with sound vs without sound), and their interaction. ▪ Subject will be included as a random effect with a random intercept to account for interindividual differences in baseline sleepiness. ▪ Where model convergence permits, random slopes for condition effects may be explored. ▪ Conduct planned comparison [50] to examine differences in subjective sleepiness between human and digital yawning stimuli, differences between auditory conditions (with vs without sound), and the interaction between stimulus type and auditory condition.
Secondary outcome analysis	▪ Apply the mixed-effects modeling framework used for primary outcome analysis to each physiological outcome, including HRV, EDA, skin temperature, pupil dynamics, and fNIRS measures. ▪ Analyses will focus on changes relative to baseline and associations with experimental conditions. ▪ Where appropriate, multiple comparison adjustments (e.g., Bonferroni or false discovery rate correction) will be reported as supplementary information.
Exploratory analysis	▪ Examine sleep onset occurrence and sleep onset latency based on behavioral and physiological indicators. ▪ Count observable yawning events by condition. ▪ Examine the relationship between yawning frequency and outcome measures (KSS scores and physiological measures) using mixed-effect models. ▪ Where temporal resolution permits, conduct event-based analyses to examine short-term physiological responses surrounding yawning events. ▪ Explore moderation effects by including interaction terms in mixed-effects models (e.g., chronotype, habitual sleep quality, baseline sleepiness, and personality traits).
Model diagnostics	▪ Inspect Q-Q plots of residuals to assess normality. ▪ Plot residuals vs fitted values to check homoscedasticity. ▪ Use formal diagnostic tests where appropriate (Shapiro-Wilk, Breusch-Pagan). ▪ Report any violations and their potential impact on inference and apply transformations if necessary.

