## Description of protocol

### Overview

This protocol employs a laboratory-based, randomized within-subject crossover experimental design to examine the associations between contagious yawning stimuli exposure and subjective and physiological indicators of sleepiness. The protocol follows a 2 × 2 factorial structure manipulating: (1) stimulus type (human vs. digital character yawning) and (2) auditory content (with vs. without sound), yielding four experimental conditions.

Participants complete two sessions on separate days. In one session, they view human yawning videos under both auditory conditions in randomized order. In the other session, they view yawning videos of digital characters under the same auditory conditions. The order of sessions (human first vs. digital first) will be counterbalanced across participants. The order of conditions will be randomized and counterbalanced to minimize systematic order effects.

A within-subject design was selected to maximize sensitivity to condition-related differences while controlling for interindividual variability in baseline sleepiness, circadian preference, and autonomic functioning. To mitigate potential fatigue or habituation effects, experimental sessions will be conducted on separate days with a minimum interval of one-day between sessions.

The protocol is designed to examine relative differences across yawning stimulus conditions and within-subject changes over time, rather than to isolate yawning-specific causal effects relative to neutral stimulus exposure. Accordingly, non-yawning control conditions are not included. This design enables focused comparison across stimulus modalities and representations while maintaining a manageable experimental duration within a multimodal physiological recording context, which is consistent with prior studies using contagious yawning stimuli [26,27]. Pre-stimulus baseline recordings will be obtained prior to each condition, which allows within-subject quantification of changes relative to a stable resting reference.

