#### Experimental procedure

Each experimental session includes two yawning stimulus conditions (with sound and without sound) presented in randomized, counterbalanced order. To minimize social presence effects on yawning responses [40,23], participants will remain alone in the experimental room throughout stimulus presentation, while the experimenter monitors the session remotely from an adjacent space via a live physiological data feed and video stream.

At the beginning of each condition, physiological recording will begin continuously, and participants will be instructed to watch the videos naturally and to maintain a comfortable and relaxed posture. No further instructions regarding yawning will be given at this stage, as participants will have been informed of their freedom to respond naturally at the pre-session assessment stage.

Stimulus presentation will then proceed for approximately 5 min. Each stimulus sequence will consist of approximately 50 discrete yawning events, each approximately 6 s in duration [41,42]. This duration is consistent with prior experimental yawning paradigms in contagious yawning research and falls within the commonly used 3–5 min exposure range [15,22]. During this period, all physiological signals will continue to be recorded continuously, and participant behavior will be monitored via the video recording. Particular attention will be given to signs of sleep onset such as sustained eye closure. If sleep onset occurs, the corresponding timestamp will be noted, and recording will continue without interruption.

Following stimulus presentation, a post-condition assessment period of approximately 10 min will be conducted. Video will be stopped, and subjective sleepiness will be assessed using the KSS. Participants will also complete a brief questionnaire regarding their yawning behavior, including whether they yawned or experienced an urge to yawn [40].

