### Yawning stimulus materials

Human yawning stimuli will be compiled from publicly available video recordings, drawing on sources such as YouTube (the “yawn-o-meter”), TikTok, and the YawnStim dataset [43]. Clips will be selected based on clear visibility of facial expressions and the presence of naturalistic yawning behavior. Each condition will include approximately 50 discrete, non-repeating yawning events, each lasting 6 s [41,42], resulting in a total stimulus duration of 5 min. The final stimulus set will include a balanced representation of male and female individuals.

Digital character yawning stimuli will be generated using generative AI tools to produce controlled yet diverse animated yawning clips. Stylized animal-like characters (e.g., cats and dogs) will be used to reduce potential confounds associated with human identity, attractiveness, or familiarity, while preserving clearly recognizable yawning behavior. Animal-like characters were selected because they are sufficiently human-dissimilar to avoid uncanny valley effects, yet sufficiently familiar to elicit socially contagious responses, consistent with prior evidence that contagious yawning occurs across species [44]. Each clip will be structured to reflect the typical temporal phases of a yawn, including gradual mouth opening, peak extension, and closure, with smooth motion transitions. Slight variations in timing and motion will be introduced to maintain naturalness while avoiding repetition. All generated clips will undergo manual selection and standardization to ensure experimental consistency. Clips with ambiguous expressions, unnatural motion, or technical artifacts will be excluded. Remaining clips will be standardized in duration, resolution, and presentation format.

For audiovisual conditions, yawning sounds will be synchronized with the peak mouth-opening phase of each clip, while silent conditions will use identical clips without audio. For the human yawning clips with audio, the original audio from the source clips will be retained. For digital pet clips and human yawning clips without audio, yawning sounds will be synthesized using audio generation tools. Generated sounds will be standardized in amplitude and duration and evaluated for perceived naturalness prior to use. Stimulus sequences will be matched across human and digital pet conditions in terms of the number of yawns, inter-yawn intervals, and total duration.

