### Limitations

Several limitations should be acknowledged. First, the laboratory-based setting may limit ecological validity relative to real-world contexts in which yawning and sleepiness naturally occur. Second, the protocol does not include a non-yawning control condition. Although baseline and post-condition measurements allow for within-subject assessment of state changes, the absence of a neutral comparison condition limits the ability to attribute observed changes uniquely to yawning stimuli, as alternative explanations such as time-on-task effects, fatigue, or repeated exposure cannot be fully excluded. Third, while behavioral indicators of sleep onset and physiological correlates of reduced arousal will be assessed, the study does not include polysomnography. Therefore, precise sleep onset latency cannot be determined. Despite these limitations, this protocol establishes a methodological framework for investigating how human-like behavior presented by digital agents is associated with subjective and physiological states, which provides a foundation for future confirmatory studies and real-world deployments.

Findings from executing this protocol will have several important implications. From a theoretical perspective, it contributes to a more functional understanding of whether exposure to contagious yawning stimuli is associated with changes in sleepiness and arousal regulation, rather than focusing solely on yawning frequency. By integrating subjective, physiological, and behavioral indicators, the study informs ongoing debates regarding the potential role of yawning stimuli exposure in sleep-related state modulation. From an applied perspective, the findings may inform the design of non-pharmacological approaches for modulating arousal and relaxation. In particular, evidence that digitally presented yawning stimuli are associated with sleepiness-related responses would have implications for the design of AI-driven avatars, digital companions, and interactive health technologies, where subtle behavioral cues may be leveraged to influence user state without explicit instruction.

Importantly, even in the absence of strong effects, the study will help delineate the conditions under which exposure to contagious yawning stimuli is not meaningfully associated with sleepiness-related states. Such null or weak findings would provide valuable insight for refining theoretical models and informing the design of future digital interventions.

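### The primary model omits session number and position within session, although the design randomises or counterbalances both; any order effect then inflates the residual, and shifts the contrasts if the analysed orders are unequal

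*Protocol article*

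**What the plan says.** The protocol article describes a 2 × 2 within-subject crossover. Stimulus type changes between two sessions on separate days; sound changes within a session.

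- Overview, on sessions: "The order of sessions (human first vs. digital first) will be counterbalanced across participants". The section on Phase 2 calls the same order randomised.
- Overview, on the purpose: "The order of conditions will be randomized and counterbalanced to minimize systematic order effects".
- Experimental procedure, on sound: "Each experimental session includes two yawning stimulus conditions (with sound and without sound) presented in randomized, counterbalanced order".
- Data analysis, Table 2, primary outcome: "Fixed effects will include stimulus type (human vs digital character yawning), auditory condition (with sound vs without sound), and their interaction". On random effects: "Subject will be included as a random effect with a random intercept to account for interindividual differences in baseline sleepiness". Random slopes for condition are optional.

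Table 2 applies the same framework to each physiological outcome. No session, position or sequence term appears in either row. Time is mentioned as a possible within-subject factor only in the paragraph on exploratory relationships.

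**The concern.** The design treats order as worth controlling, but the stated model ignores it. Several features of the procedure make an order effect plausible:

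- The first film follows quiet set-up and a seated baseline. The second follows a reset of about 15 minutes with brighter light and movement.
- A questionnaire on yawning and the urge to yawn comes after the first film, and so before the second.
- On stimuli, the article says that "silent conditions will use identical clips without audio", so the second film appears to repeat the clips of the first.
- The focus on yawning is withheld only until stimuli are shown, so session 2 starts with participants who have already seen them.

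Two things are at stake. Variation due to order that could be modelled goes into the residual and widens the intervals for sound and stimulus type. And if the analysed data do not contain equal numbers in each order, part of the order effect is read as a condition effect.

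**Working it through.** **Inputs from the article.** Four post-condition KSS ratings per participant (two stimulus types by two sound conditions); the Table 2 model; two-sided alpha 0.05. The article gives no sample size, residual SD, loss rate or order effect, so there is no figure of its own to reproduce.

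**Assumptions for illustration.** 30 participants, residual SD s = 1 KSS point, no true condition effect, no extra variance between sessions. P is the effect of second against first position; T is the effect of session 2 against session 1.

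**Step 1: balanced orders.** Each rating departs from the participant's mean by ±P/2 for position and ±T/2 for session. Over four ratings this adds 4 × P²/4 + 4 × T²/4 = P² + T² to the within-participant sum of squares; the cross-products cancel. With three within-participant degrees of freedom, the estimated residual variance is multiplied by about 1 + (P² + T²)/(3s²):

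- P = 0.5, T = 0: 1 + 0.25/3 = 1.08
- P = 1, T = 0: 1 + 1/3 = 1.33
- P = 1.5, T = 0: 1 + 2.25/3 = 1.75
- P = T = 0.5: 1 + 0.5/3 = 1.17
- P = T = 1: 1 + 2/3 = 1.67

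Without order effects the standard error of either main contrast is √(1/30) = 0.183. It becomes 0.183 × √1.17 = 0.197 for P = T = 0.5, and 0.183 × √1.67 = 0.236 for P = T = 1. The true sampling SD stays near 0.18, because balance cancels the order effect in the estimate. So the reported error is too large and the test is conservative.

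**Step 2: unequal orders.** Within a session, the sound-minus-silent difference is the true effect + P if sound comes second and − P if it comes first. With share q of sessions having sound second, the shift is qP − (1 − q)P = (2q − 1)P. The same form holds for stimulus type with T. At 60/40 the shift is 0.2 times the order effect; at 20/10 it is (20 − 10)/30 = 0.33 times.

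**Step 3: simulation.** 1,500 runs per setting, using the within-participant estimator, which equals the random-intercept estimator for these contrasts in complete data. The split applies to session order and to sound order. Each cell gives stimulus type / sound; bias is in absolute KSS points.

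| Split | P = T | Bias, Table 2 model | Type I error, Table 2 model | Type I error, session and position added |
|---|---|---|---|---|
| 15/15 | 0.5 | 0.004 / 0.011 | 2.7% / 3.9% | 4.7% / 4.9% |
| 15/15 | 1 | 0.009 / 0.001 | 1.0% / 1.1% | 6.2% / 5.4% |
| 18/12 | 0.5 | 0.103 / 0.087 | 5.8% / 4.9% | 5.6% / 4.9% |
| 18/12 | 1 | 0.201 / 0.207 | 7.4% / 7.5% | 4.9% / 4.7% |
| 20/10 | 0.5 | 0.170 / 0.171 | 11.1% / 14.3% | 4.6% / 5.6% |
| 20/10 | 1 | 0.334 / 0.335 | 25.7% / 25.5% | 3.9% / 5.1% |

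With the two terms added, bias is at most 0.01 point and the mean standard error is 0.18 to 0.19 in every setting.

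**Step 4: how the orders could become unequal.** If session order were assigned by simple randomisation, 30 participants would split 18/12 or worse about 36% of the time. Participant selection and the pre-session assessment re-check eligibility at each session, including a baseline KSS of 7 or more. Phase 3 lets participants withdraw their data.

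**The case against.** The strongest reply is that counterbalancing already protects the contrasts. In balanced complete data that is right: a reader might infer that leaving out the order terms biases the comparison in itself, and it does not. What remains is lost precision, and that needs only an order effect.

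Second, imbalance may be mild and harmless on average. The eligibility re-check precedes any film that day, so it has no evident link to sound order, and between films a drowsy participant gets a longer reset and is not excluded. Losses unrelated to order average to zero over randomisations. If sound order were reversed between a participant's two sessions, position would cancel within the participant; the article does not fix that scheme. All this stands, but a shift in the one realised sample would still be there, and the two terms remove it.

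Third, the order effects may be small. Sessions are on separate days at similar times, the reset ends with a KSS check, and if change is measured from that rating, a shift in level partly cancels. Participants are also told at the start of each session that they are free to yawn, which weakens the contrast in awareness between sessions. This is fair: P and T are unknown.

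Fourth, the wording on fixed effects need not be exhaustive, and an analysis plan that is not shown could add terms. But Table 2 specifies the primary model down to optional random slopes, and nothing in the article signals an order term.

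**Conclusion.** The concern holds as a recommended improvement to a stated model. Under balance, inference is unbiased but conservative, with residual variance inflated by about a third for P = s = 1 and T = 0. Under imbalance, the realised contrast moves by (2q − 1) times the order effect. Both sizes depend on assumed values of P, T and s, and the error rates also on an assumed 30 participants.

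Three stronger readings are tempting and not supported.

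- A reader might use 1 + P²/(2s²), which gives 1.50 at P = s = 1. That is the variance inflation for a paired sound-minus-silent difference; Table 2 pools one residual over four ratings, which gives 1.33.
- A reader might infer that sleep-onset and artefact exclusions unbalance the primary outcome. Data pre-processing frames those rules around physiological signals. They bear on the secondary models and do not clearly remove KSS ratings.
- A reader might take the Limitations section to concede large order effects. It says that "alternative explanations such as time-on-task effects, fatigue, or repeated exposure cannot be fully excluded", but in the context of lacking a neutral control. It makes such effects plausible without saying how large they are or that they differ between conditions.

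**What to change.** In Table 2, add session number (1 or 2) and position within session (1 or 2) as fixed effects to the primary KSS model and to the secondary physiological models. Both factors are known from the randomisation. The cost is about two degrees of freedom, and fixing the terms before data are seen avoids a later choice between models.

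A sound-by-position term may be added as a sensitivity analysis for unequal carryover within a session. A type-by-session term should not be offered as a carryover test: with two session orders it is aliased with sequence (human first or digital first). An analysis of only the first film of session 1 is descriptive at most, because it makes every contrast between-subject and uses a quarter of the ratings.

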#### Pre-session sleep quality and baseline sleepiness assessment

At the beginning of the session, participants will be greeted and their readiness to proceed will be confirmed. Sleep quality from the previous night, as measured by a smartwatch, will be reviewed. Baseline sleepiness will be assessed using the KSS. These data will be used to verify that the participant does not meet the exclusion criteria. Participants will then be instructed to observe the stimuli naturally without performing any explicit task. They will also be informed that they are free to yawn (or not) according to their natural inclination throughout the session, including during baseline recording.

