Finally, a video camera will be positioned to capture the participant’s facial expressions throughout the session. The camera angle will be adjusted to ensure a clear view of the face, and ambient lighting will be optimized to support subsequent behavioral coding. A brief test recording will be conducted to confirm that facial features are clearly visible.

To ensure consistency across participants, the experimental environment will be standardized. Room temperature will be maintained between 20 and 22 °C throughout the session. Lighting conditions will be controlled at a moderate and consistent level. External noise and potential interruptions will be minimized as much as possible. Participants will be seated comfortably in a chair with back support, and the display screen will be positioned at eye level and at an appropriate viewing distance to reduce physical strain.

Following equipment setup, a five-minute baseline physiological recording will be conducted. This duration was selected based on prior studies examining the signal lengths required to reliably derive downstream physiological and cognitive indices [[37], [38], [39]]. Participants will be instructed to sit quietly in a reclining chair and relax while maintaining their gaze on a neutral fixation point displayed on the screen. All physiological signals will be recorded continuously during this period. To avoid introducing confounding influences, no conversation or additional instructions will be provided during the baseline recording.

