#### Data storage and security

All data collected in this study will be handled in accordance with strict data protection and ethical guidelines. To protect participant privacy, data anonymization will be implemented at the time of enrollment. Each participant will be assigned a unique anonymous code, which will be used to label all data files. All physiological data files will be kept on a password-protected offline computer, while questionnaire data will be stored in encrypted digital formats. Video recordings will be stored only temporarily on a secure offline device for the sole purpose of behavioral feature extraction, such as identifying yawning occurrences and sleep onset timing. Once these behavioral codes have been extracted, all video recordings will be permanently deleted. Only the derived behavioral codes will be retained, and these will be incorporated into a fully de-identified dataset for analysis. Consistent file naming conventions (e.g., “ID_SessionNumber_Condition_DataType_Date”) will be used throughout the study to facilitate data processing, improve traceability, and reduce the likelihood of handling errors.

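### The planned yawn count has no resting level, so the plan gives no estimate of yawning during the films relative to rest, although the filmed 5-min rest could supply one

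*Protocol article*

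**What the plan says.** Table 2 of the protocol article (Data analysis, exploratory row) plans to "Count observable yawning events by condition" and then to relate yawning frequency to KSS and physiology in mixed-effects models. The Overview defines the conditions through the 2 x 2 design of stimulus type and sound, "yielding four experimental conditions". Rest is not one of them. Data pre-processing specifies baseline correction for the physiological measures and says nothing of the kind for yawn counts.

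The rest period is described under Equipment and environment setup: "Following equipment setup, a five-minute baseline physiological recording will be conducted". The camera is set up before it: "a video camera will be positioned to capture the participant’s facial expressions throughout the session". Participants are told that they are "free to yawn (or not) according to their natural inclination throughout the session, including during baseline recording". On the video, Data storage and security says: "Once these behavioral codes have been extracted, all video recordings will be permanently deleted".

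The Overview justifies having no non-yawning control partly by the resting recordings, which it says "allows within-subject quantification of changes relative to a stable resting reference". The same sentence begins "Pre-stimulus baseline recordings will be obtained prior to each condition", whereas the setup section describes one recording, after equipment setup.

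**The concern.** Physiology is read against rest. Yawning, the behavior most directly tied to the stimuli, has no resting comparison in the plan, although the material for one is already being filmed. Counts by film show how much people yawned during each film and how the films differ. They do not show how much of that yawning would have occurred while sitting quietly.

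Two uses of the data are affected. First, the Limitations section says that null or weak findings would still be informative about when exposure is not associated with sleepiness. Such a result is easier to read if one knows whether yawning during the films was any more frequent than at rest. Second, the yawning-frequency models relate film yawns to KSS and physiology. Without a resting count, a person's general tendency to yawn, which may itself follow sleepiness, cannot be separated from yawning during the film.

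Most gaps in an exploratory analysis can be repaired after the data are in. This one cannot be repaired if rest has not been coded by the time the video is deleted.

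**Working it through.** The protocol article states no sample size, yawn rate or power for this outcome, so there is no figure of the plan's to reproduce. The inputs below are from the documents unless marked as assumed.

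**1. Window lengths.** One film is about 50 yawns of 6 s (Experimental procedure; Yawning stimulus materials): 50 x 6 s = 300 s = 5 min. One rest is 5 min. The two windows are equal, so counts can be compared without rescaling.

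**2. What counts by film leave open.** Assume a mean of 1 yawn per film. The film-to-rest ratio is then 1 divided by the resting mean per 5 min:

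| Assumed resting mean | Film-to-rest ratio |
|---|---|
| 0.1 | 10 |
| 0.25 | 4 |
| 0.5 | 2 |
| 1.0 | 1 |
| 1.5 | 0.67 |

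Every row is compatible with the same table of counts by condition. The planned count therefore carries no information on this ratio.

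**3. Rest exposure under the two descriptions of the baseline.** Film time is 2 sessions x 2 films x 5 min = 20 min per participant.
- One rest per session (setup section): 2 x 5 = 10 min of rest. With equal rates, 20/(20+10) = 66.7% of yawns would fall in the films.
- One rest before each condition (Overview): 4 x 5 = 20 min of rest. With equal rates, 20/(20+20) = 50% would fall in the films.

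The expected split under no difference thus depends on which description is right.

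**4. Precision if rest were coded.** Take one film-rest pair per participant, scored as any yawn or none. Let p10 be the proportion yawning only during the film and p01 the proportion yawning only at rest. The excess is p10 − p01, with SE = sqrt((p10 + p01 − (p10 − p01)²)/N) and 95% half-width 1.96 x SE. N, p10 and p01 are all assumed.
- p10 = 0.30, p01 = 0.05, N = 40: SE = sqrt((0.35 − 0.0625)/40) = 0.0848, so the excess is 25 ± 16.6 points.
- p10 = 0.20, p01 = 0.10, N = 40: SE = sqrt((0.30 − 0.01)/40) = 0.0851, so the excess is 10 ± 16.7 points.
- For the same two cases the half-width is about 21.5 points at N = 24 and about 11.8 at N = 80.

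A large excess would be visible at these sizes, and a modest one would not be resolved.

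**The case against.** The strongest reply is that the article condenses a fuller plan, and the coding window of an exploratory behavioral count may well be set elsewhere. The article also does not confine coding to the films. Table 1 gives the timing of the video data as the experimental sessions, and the Data analysis text speaks of yawning seen during the experiment. A reader might infer from Table 2 that yawns are counted only during the films; that goes beyond the text. A reader might also infer that deletion makes a resting count impossible. It does not: deletion follows feature extraction and the codes are kept. Both replies stand. What remains is that the analysis level is stated, rest is not in it, and nothing secures the coding of rest before the video is gone.

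The second reply is that the protocol does not claim that its films raise yawning. Its research questions concern sleepiness, it disclaims yawning-specific causal effects, and it lists the missing control as a limitation. This also stands, and it limits what a resting count can be for. A reader might say that the trial cannot show its films raised yawning and that a resting count would put this right. It would not. Rest always precedes the first film, it uses a fixation point and not a video, and the article promises that participants are alone only during stimulus presentation. A film-rest difference mixes all of these.

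Nor is it right that a flat KSS result would be uninterpretable without the resting count. The post-condition questionnaire asks about yawning and the urge to yawn, and very few film yawns would be informative in themselves. Likewise, the yawning-frequency models are described as examining relationships, not as attributing yawns to the films. Finally, baseline KSS is taken before equipment setup and the rest, so the resting recording is not the reference for KSS.

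**Conclusion.** The point holds as a gap in an exploratory analysis that is cheap to close. The one planned yawn count has no resting level, and the plan as written yields no estimate of yawning during the films relative to rest. The resting recording is the only reference for spontaneous yawning in the design, it is as long as one film, and it is already on camera. No primary or secondary result is affected.

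The size can be given only under assumptions. The counts by film are compatible with ratios from 10 to 0.67 over the assumed resting means, and a coded rest would give the excess proportion yawning to about ±17 points at an assumed N of 40 (about ±22 at 24, ±12 at 80).

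The documents do not support saying that rest is barred from coding, that deletion by itself prevents a resting count, or that a film-rest difference would establish cause.

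**What to change.** Change the Table 2 line to say that yawns are counted by condition and in each pre-stimulus resting recording, with the same coding rules and before the video is deleted. Report film minus rest, per 5 min, for the first film of each session; this comparison is available under either description of the baseline. Include the resting count as a covariate in the exploratory yawning-frequency models. Label the result a descriptive check on the exposure, and state that it is not evidence that the films caused yawning, for the reasons of order, fixation point and possible attendance at rest.

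Reconcile the Overview with Equipment and environment setup on whether rest is recorded once per session or before each condition, since this sets the resting exposure time.

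The cost is coding time only: 2 x 5 = 10 more minutes of video per participant with one rest per session, or 4 x 5 = 20 with a rest before each condition. No new recording or visit is needed.
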